**4.5 ENROLLMENT/ALLOCATION PROCEDURES**

### 4.5.1 Enrollment

The principal investigator/subinvestigator will select and enroll subjects according to the following procedures.

1) The details of the study will be explained to the prospective participants who meet all of the inclusion criteria described in 1)–4) and do not meet any of the exclusion criteria described in 1)–13) and who provide written informed consent to participate in the study.

2) Subject candidates will be selected according to the results of the screening tests.

3) Subjects will be selected from subject candidates according to the results of the pre-administration tests.

### 4.5.2 Preparation of Screening Log/Subject Registration List

Information regarding the date of the consent process (date when the request for an informed consent and information provision was made), existence of consent, and date of the signed consent form for all prospective participants (who have requested and received the informed consent explanations) will be documented by the principle investigator in the “Screening Log/Subject Registration List (Form 1)” regardless of their consent.

Subject identification codes and gender are recorded only for those subjects who have been determined as eligible subjects and who have consented to participation.

### 4.5.3 Preparation of the Subject Identification Code List

Subject identification codes must be assigned to each subject by the principal investigator before study drug administration (subject allocation).

Furthermore, the “Subject Identification Code List (Form 2)” must be prepared separately from the “Screening Log/Subject Registration List” described above. This form must contain the subject identification code, medical record number, and subject name.

The principal investigator must use subject identification codes to identify subjects when reporting adverse events (AEs) and other study-related information.

| Fixed code - Subject number | Subject identification code (sample) |
| --- | --- |
| BR01 - 01, 02, 03, 04 | BR01-01 |

### 4.5.4 Subject Allocation

Subjects who are selected by screening and pre-dose testing will be randomly assigned (allocation ratio of 1:1:1) into 3 groups (Groups A–C) after enrolling with the central allocation system. At this time, the below-mentioned information will also be recorded in the “Subject Identification Code List (Form 2).”

(a) Eligibility

(b) Order of allocation

(c) Allocated group [Group A, B, or C]

# 5 STUDY METHOD

**5.1 STUDY DESIGN**

This is a randomized crossover study. The study drug will be administered to the same subjects after a washout period of greater than 4 weeks.

**5.2 DOSAGE AND ADMINISTRATION**

Subjects will be randomly assigned to Groups A–C after enrollment, and 3 different dosages will be administered to the same subject at 3 separate times. The 3 dosage periods will be designated as phase I, phase II, and phase III, with a washout period of greater than 4 weeks between phases I and II and between phases II and III (Table 1).

Table 1 Dosing Schedule

|  | Phase I | Washout period | Phase II | Washout period | Phase III |
| --- | --- | --- | --- | --- | --- |
| Group A | 7.5 g | >4 weeks | 2.5 g | >4 weeks | 5.0 g |
| Group B | 2.5 g | >4 weeks | 5.0 g | >4 weeks | 7.5 g |
| Group C | 5.0 g | >4 weeks | 7.5 g | >4 weeks | 2.5 g |

**5.3 STUDY COMPLETION, SUBJECT DISCONTINUATION, AND WITHDRAWAL**

### 5.3.1 Study Completion

Each treatment phase will be considered complete after blood sampling and testing at the end of 48 h after study drug administration.

The study will conclude after completion of the 3 treatment phases.

### 5.3.2 Subject Discontinuation or Withdrawal

The investigator may terminate or withdraw a subject from the study in case of the following:

1) If the subject requests withdrawal or declines participation

2) If the subject experiences an AE that undermines continuation of the study in the opinion of the principal investigator

3) If the subject is unable to take the study drug

4) If the subject is judged as ineligible to continue the study by the principal investigator

### 5.3.3 Discontinuation Procedure

The principal investigator/subinvestigator must document the reason(s) for discontinuation, measures taken, and follow-up in the Case Report Form (CRF). If discontinuation is for safety reasons, appropriate measures must be taken and the subjects should be followed-up to resolution until their safety is assured, except in cases where consent cannot be obtained from the subjects.

### 5.3.4 Subject Replacement

Subjects will be replaced if discontinuation or withdrawal results in a sample size that falls below the required size for the study (15 subjects). The number of withdrawn subjects will be replaced, and the subjects will undergo test procedures beginning from phase I according to their allocated group. Samples collected from participants until discontinuation may be used for analysis as long as consent is obtained from the withdrawn subjects.

### 5.3.5 Management of Subjects

All subjects are under close supervision of the principal investigator/subinvestigator during their participation in the clinical study.

The principal investigator/subinvestigator will instruct all subjects to comply with the following directions.

1) Foods and drinks

Foods and drinks containing caffeine, alcohol, citrus fruits (grapefruit, orange, tangerine, etc.), vitamin P, Ginseng, Ginger, Glycyrrhiza (listed on a food label) and garlic (including spices) (see attached reference) are prohibited from 3 days prior to study drug administration until completion of each treatment phase of the study. Supplements containing constituents of rikkunshito (Atractylodes Lancea Rhizome, Ginseng, Pinellia Tuber, Poria Sclerotium, Jujube, Citrus Unshiu Peel, Glycyrrhiza,

Ginger), Processed Ginger, and vitamin P are also prohibited. However, foods and drinks that do not contain the above (see attached references) may be consumed at any time. Subjects must have fasted from 20:00 on the eve of study drug administration to 4 h post-dose.

2) Smoking

Smoking is prohibited from 3 days prior to study drug administration until completion of each treatment phase of the study.

3) Use of other drugs

Use of other drugs is prohibited from 7 days prior to study drug administration until completion of each treatment phase of the study.

# 6 CLINICAL STUDY MATERIAL

# 6.1 PROPRIETARY NAME AND MANUFACTURER

Study drug: Tsumura Rikkunshito Extract Granule (for prescription)

Code number: TJ-43

Manufacturer: Tsumura & Co.

## **6.2 CONSTITUENTS, DOSAGE FORM, STORAGE**

Constituents/Content: 7.5 g of TJ-43 contains 4.0 g of dried extract of the following ratio of crude drugs.

JP Atractylodes Lancea Rhizome 4.0 g JP Jujube 2.0 g

JP Ginseng 4.0 g JP Citrus Unshiu Peel 2.0 g

JP Pinellia Tuber 4.0 g JP Glycyrrhiza 1.0 g

JP Poria Sclerotium 4.0 g JP Ginger 0.5 g

(JP: The Japanese Pharmacopoeia)

Additives: JP Magnesium Stearate, JP Lactose Hydrate, Sucrose Esters of Fatty Acids

Dosage form: Granules

Packaging: One heat-sealed sachet contains 2.5 g of extract granules

Storage: Store in a cool, dry place. Avoid contact with moisture and direct sunlight.

**6.3 DOSAGE AND ADMINISTRATION METHOD**

Single oral administration of TJ-43 at doses of 7.5 g (1 sachet 2.5 g × 3 sachets), 5.0 g (1 sachet 2.5 g × 2 sachets), and 2.5 g (1 sachet 2.5 g × 1 sachet)

[Rationale for Dosage]

In this study, the doses of 7.5 g, 5.0 g, and 2.5 g (at a constant difference of 2.5) have been selected on the basis of the following 3 conditions.

A total of 7.5 g is usually administered over 2 or 3 doses daily.

1. Determination of the maximum dose of 7.5g that is well tolerated in subjects as a single dose

AEs associated with TJ-43 did not occur after single oral administration of 7.5 g TJ-43 in a previously conducted preliminary pharmacokinetics study19).

1. Determination of the minimum dose of 2.5 g based on TJ-43 dosage and administration

The minimum dose of TJ-43 has been set at 2.5 g, which is the average prescribed single dose.

1. Measurability of concentrations

Based on the results of the preliminary pharmacokinetics study19), measurement of TJ-43 constituents in plasma is probable with the minimal administration dosage of 2.5 g due to the improved and sensitive analytical method.

The maximum plasma concentration of each constituent in the preliminary pharmacokinetics study19) (7.5 g dosage) was 0.228 ± 0.116 ng/mL for pachymic acid, 0.0475 ± 0.0297 ng/mL for isoliquiritigenin, 1.84 ± 0.626 ng/mL for atractylodin, 0.0626 ± 0.0436 ng/mL for nobiletin, 0.253 ± 0.301 ng/mL for heptamethoxyflavone, 0.162 ± 0.0392 ng/mL for naringenin, and 64.7 ± 11.8 ng/mL for glycyrrhetinic acid. The lower limits of quantitation for the constituents are 0.1 ng/mL for pachymic acid, 0.02 ng/mL for isoliquiritigenin, 1 ng/mL for atractylodin, 0.02 ng/mL for nobiletin, 0.02 ng/mL for heptamethoxyflavone, 0.1 ng/mL for naringenin, and 0.1 ng/mL for glycyrrhetinic acid.

**6.4 SUPPLY AND DELIVERY**

The clinical study material will be supplied and delivered by the sponsor to the institution for free after the study contract is signed between the two parties.

**6.5 STORAGE AND HANDLING**

The study drug administrator will store and handle the clinical study material in an appropriate manner.

**6.6 RETRIEVAL**

The study drug administrator will retrieve all unused clinical study material after inspection by the sponsor.

**7 TESTS, EVALUATIONS, AND TEST PERIOD**

**7.1 TEST AND EVALUATION ITEMS**

**7.1.1 Screening Items**

The principal investigator/subinvestigator will conduct the following medical interview, clinical observations, and laboratory tests 1 week prior to the start of the trial and select prospective subjects on the basis of the test results. The screening date’s margin of error is ±1 day.

Demographics: date of birth, gender, race, present illness, current medications, history of drug and food allergies, past medical history, alcohol intake, smoking history

Clinical findings: subjective symptoms, objective findings, edema

Physical examination: height, weight, BMI, body temperature (axillary), blood pressure (seated), pulse (seated)

Laboratory tests: 1) Hematology

erythrocytes, leukocytes, platelets, hemoglobin, hematocrit

2) Blood chemistry

total protein, BUN, creatinine, uric acid, AST, ALT, T-Bil, ALP, γ-GTP, Alb, PT, TC, CRP, HbA1c, K

3) Urinalysis

urine sugar

Urine pregnancy test (female)

Viral tests: HCV antibody, HBs antigen, HIV antibody

**7.1.2 Pre-dose Tests**

The principal investigator/subinvestigator will perform the following clinical observations and laboratory tests 1 day prior to study drug administration and select prospective subjects on the basis of comprehensive analysis of the test results.

Clinical findings: subjective symptoms, objective findings, edema

Physical examination: body temperature (axillary), blood pressure (seated), pulse (seated)

Laboratory tests: 1) Hematology

erythrocytes, leukocytes, platelets, hemoglobin, hematocrit

2) Blood chemistry

total protein, BUN, creatinine, uric acid, AST, ALT, T-Bil, ALP, γ-GTP, Alb, PT, TC, CRP, K

Urine pregnancy test (female): At the time of screening in phase I

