**7.2 SCHEDULE OF TIME AND EVENTS**

Each laboratory test and clinical observation will be performed according to the study schedule in Table 2

Table 2 Study schedule

|  | Day-7 | Phase I | | >4  weeks | Phase II | | >4  weeks | Phase III | |
| --- | --- | --- | --- | --- | --- | --- | --- | --- | --- |
| 1-Day-1 | 1-Day0~1-Day+2 | Washout Period | 2-Day-1 | 2-Day0 ~  2-Day+2 | Washout Period | 3-Day-1 | 3-Day0~  3-Day+2 |
| Screening | Pre-dose | Dosing and  blood sampling  (until 48 h) | Pre-dose | Dosing and blood sampling (until 48 h) | Pre-dose | Dosing and blood sampling  (until 48 h) |
| Informed consent | 〇 |  |  |  |  |  |  |
| Enrollment |  | 〇 |  |  |  |  |  |
| Allocation |  | 〇 |  |  |  |  |  |
| Demographics | 〇 |  |  |  |  |  |  |
| Height, weight, BMI | 〇 |  |  |  |  |  |  |
| Blood pressure, pulse, body temperature | 〇 | 〇 | 〇 | 〇 | 〇 | 〇 | 〇 |
| Clinical examination | 〇 | 〇 | 〇 | 〇 | 〇 | 〇 | 〇 |
| Urine pregnancy test | 〇 |  |  | 〇 |  | 〇 |  |
| Lab tests | 〇 | 〇 | 〇 | 〇 | 〇 | 〇 | 〇 |
| TJ-43 administration  Group A  Group B  Group C |  |  | 〇  7.5 g  2.5 g  5 g |  | 〇  2.5 g  5 g  7.5 g |  | 〇  5 g  7.5 g  2.5 g |
| Pharmacokinetics |  |  | 〇 |  | 〇 |  | 〇 |
| Safety  assessment |  |  |  |  |  |  |  |  |  |

Each laboratory test and clinical observation will be performed according to the study schedule in Table 3 (sample time schedule is shown).

Table 3 Study Schedule 2 (each phase)Note1

|  | Day  -7 | Day  -1 | Day 0 | | | | | | | | | | | | Day  +1 | Day  +2 |
| --- | --- | --- | --- | --- | --- | --- | --- | --- | --- | --- | --- | --- | --- | --- | --- | --- |
| Screening | Pre-dosing | Immediately before dosing | 0  h | 15  min | 30  min | 1  h | 2  h | 3  h | 4  h | 6  h | 8  h | 10  h | 12  h | 24  h | 48  h |
| 7:  30 | 8:  00 | 8:  15 | 8:  30 | 9:  00 | 10:00 | 11:00 | 12:00 | 14:00 | 16:00 | 18:00 | 20:00 | 8:  00 | 8:  00 |
| Informed consent | ○ |  |  |  |  |  |  |  |  |  |  |  |  |  |  |  |
| Subject roster |  | ○ |  |  |  |  |  |  |  |  |  |  |  |  |  |  |
| Allocation |  | ○ |  |  |  |  |  |  |  |  |  |  |  |  |  |  |
| Demographics | ○ |  |  |  |  |  |  |  |  |  |  |  |  |  |  |  |
| Height, weight,  BMI | ○ |  |  |  |  |  |  |  |  |  |  |  |  |  |  |  |
| Blood pressure, pulse,  body temperature | ○ | ○ |  |  |  |  |  |  |  |  |  |  |  |  |  | ○ |
| Clinical examination | ○ | ○ |  |  |  |  |  |  |  |  |  |  |  |  |  | ○ |
| Urine pregnancy testNote2 | ○ | |  |  |  |  |  |  |  |  |  |  |  |  |  |  |

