| Lab testsNote3  sample volume | ○  8 mL | ○  8 mL |  |  |  |  |  |  |  |  |  |  |  |  |  | ○  8 mL |
| TJ-43 dosing |  |  |  | ○ |  |  |  |  |  |  |  |  |  |  |  |  |
| MealNote4 |  | ○ |  |  |  |  |  |  |  | ○ |  |  | ○ |  | ○ | ○ |
| PKNote3  sample volume |  |  | ○  12 mL |  | ○  12 mL | ○  12 mL | ○  12 mL | ○  12 mL | ○  12 mL | ○  12 mL | ○  12 mL | ○  12 mL | ○  12 mL | ○  12 mL | ○  12 mL | ○  12 mL |
| Safety assessment |  |  |  |  |  |  |  |  |  |  |  |  |  |  |  |  |

Note 1: The schedule is for phase I. Screening tests conducted 7 days prior to administration of TJ-43 will not be performed in phases II and III, whereas pre-dose tests conducted 1 day prior to administration and other tests scheduled thereafter will be performed.

Note 2: This will be conducted in females only. It will be performed at the time of screening in phase I. It will be conducted 1 day prior to administration of J-43 in phases II and III.

Note 3: The total blood drawn will be 524 mL {screening: 8 mL × 1, 172 mL for each of the 3 phases [(8 mL × 2 for laboratory tests, 12 mL × 13 for pharmacokinetic) × 3]}. In addition, general urinalysis (urine sugar) will be performed at the time of screening only.

Note 4: Foods and drinks (including spices) (see attached reference) containing caffeine, alcohol, citrus fruits (grapefruit, orange, tangerine, etc.), vitamin P, ginseng, ginger, kanzo (listed on a food label), and garlic are prohibited from 3 days prior to study drug administration until completion of each treatment phase of the study. Supplements containing constituents of rikkunshito (Atractylodes Lancea Rhizome, Ginseng, Pinellia Tuber, Poria Sclerotium, Jujube, Citrus Unshiu Peel, Glycyrrhiza, and Ginger), Processed Ginger, and vitamin P are also prohibited. However foods and drinks that do not contain the above (see attached references) may be consumed at any time. Subjects must have fasted from 20:00 on the eve of study drug administration to 4 h post-dose.

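### Optional safety improvement: the phase I pregnancy test is 6 to 8 days old at the first dose, and the existing Day -1 visit could renew it at almost no cost

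*Protocol*

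**What the plan says.** All places in the Protocol that fix the phase I timing agree.

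- Section 7.1.1 lists the urine pregnancy test among the screening items, one week ahead, and says the screening date's "margin of error is ±1 day".
- Section 7.1.2, on the tests one day before dosing, has only this line on pregnancy: "Urine pregnancy test (female): At the time of screening in phase I".
- Table 2 in section 7.2 marks the test at screening, 2-Day-1 and 3-Day-1, and leaves 1-Day-1 blank.
- Note 2 to Table 3 says of phase I: "It will be performed at the time of screening in phase I". For the later phases it says: "It will be conducted 1 day prior to administration of J-43 in phases II and III".
- Note 1 to Table 3 counts screening as 7 days before TJ-43 and says it is not repeated in phases II and III.

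The Day -1 visit decides entry. Section 4.5.1, item 3: "Subjects will be selected from subject candidates according to the results of the pre-administration tests". Section 4.5.4: "Subjects who are selected by screening and pre-dose testing will be randomly assigned". Pregnancy is exclusion criterion 2 in section 4.4, and the rationale there gives subject safety as the purpose of criteria 1 to 5.

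**The concern.** Pregnancy status can change between screening and dosing. The protocol has a visit one day before the first dose at which eligibility is settled, and it repeats most screening laboratory tests there, but not the test for this safety exclusion. A pregnancy that became detectable between screening and 1-Day-1 would not be looked for by test before allocation and first exposure. No reason for leaving the test out is given.

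What is at stake is a small matter of subject protection in healthy volunteers, who have no treatment need for the drug. Sample size, pharmacokinetic parameters and planned analyses are untouched.

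**Working it through.** **Inputs.** Screening on Day -7 with a window of 1 day (section 7.1.1; Note 1 to Table 3; Table 2). First dose on Day 0. Pre-dose visit on Day -1 (section 7.1.2). Pregnancy tests marked at screening, 2-Day-1 and 3-Day-1 (Table 2). Target of 21 completed subjects of both sexes, sex mix not stated (sections 4.2 and 4.3). Section 7.1.1 counts the week from the start of the trial; Note 1 and Table 2 count it from dosing, and that is used here.

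**Age of the result at dosing.**
- Phase I: 7 - 1 = 6 days to 7 + 1 = 8 days.
- Phases II and III: Day -1 to Day 0 = 1 day.

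**Interval before the allocation visit.** From screening to 1-Day-1: 6 - 1 = 5 days to 8 - 1 = 7 days.

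**What 1-Day-1 repeats.** Comparing the lists in sections 7.1.1 and 7.1.2, all five hematology items are repeated, and so is every blood chemistry item except HbA1c. Urine sugar, the viral tests and the pregnancy test are not. Of these and HbA1c, only the pregnancy test is scheduled again before a later dose.

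**Number of tests.**
- Per woman completing all phases: 3 now; 3 + 1 = 4 with the addition.
- Doses preceded by a Day -1 test: 2 of 3 now; 3 of 3 with the addition.
- Extra tests: one per woman reaching 1-Day-1, so 0 to 21 for the target number. This is not a firm cap: section 5.3.4 restarts replacements at phase I, and some women tested on Day -1 may then not be selected.

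**Blood volume.** The stated total reproduces: 8 + 3 × (2 × 8 + 13 × 12) = 8 + 3 × 172 = 524 mL. A urine test leaves it unchanged.

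**Benefit, for scale only.** The documents give no conception risk. Assume 0.1% to 3% per 28-day cycle, with the onset of detectability spread evenly over the cycle:
- Low: 0.001 × 5/28 = 0.00018 per woman.
- High: 0.03 × 7/28 = 0.0075 per woman.
- With 10 women: 0.002 to 0.075 expected cases per trial.
- With 21 women: 0.004 to 0.16.
- With no women: 0.

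These figures rest wholly on the assumption and are not a finding about this trial. The upper end combines the highest assumed risk, the longest interval and an all-female sample.

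**The case against.** The strongest reply is that nothing here is wrong. The schedule is consistent, the protocol sets no maximum age for a pregnancy test, and nothing in it shows that a result 6 to 8 days old is inadequate before a single dose. That stands: the point is a suggestion, not a correction.

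A reader might infer from the Day -1 tests in phases II and III that the protocol holds itself to a one-day standard and breaks it in phase I. The documents do not support this. Screening is not repeated in the later phases, so Day -1 is the only visit before those doses, and the test there follows a washout of more than four weeks. The pattern fits one test at the first visit of each phase equally well.

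The risk is also limited. Exclusion 2 removes women who plan a pregnancy, symptoms and findings are checked on Day -1, and TJ-43 is a marketed product whose top single dose here equals the usual daily total (section 6.3). The package insert is cited but not included, so any fetal risk cannot be judged from the documents. All of this lowers the priority. None of it is a reason against a test that fits into an existing visit.

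**Conclusion.** The point holds as a minor, optional safety improvement. The pregnancy result is 6 to 8 days old at first exposure, and a visit that already decides selection and allocation could bring that to 1 day. The dates are certain. The benefit is very small and cannot be sized from the documents.

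Two stronger readings should be set aside. The line in section 7.1.2 might look like a contradiction, because it names screening under a heading for pre-dose tests and omits phases II and III. Table 2 and Note 2 settle the timing for all three phases, so it is only incomplete wording. Nor does the timing threaten the results: no endpoint, analysis set or comparison depends on it.

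**What to change.** - Add a urine pregnancy test for women on 1-Day-1, with a negative result required before allocation.
- Mark 1-Day-1 in the pregnancy row of Table 2, and amend Table 3 and Note 2 to match. In the text as extracted, the Table 3 mark appears to sit in a cell spanning Day -7 and Day -1, so the amended table should show the two days separately.
- Reword the line in section 7.1.2 to: *Urine pregnancy test (female): 1 day before administration in each of phases I, II and III, in addition to screening.* This also supplies the timing for phases II and III that the line now omits.

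The cost is the change of wording plus one urine test per female candidate reaching 1-Day-1: about 21 at most, slightly more with replacements or candidates not selected. It adds no visit and no blood. The same Day -1 test is already planned for phases II and III, so the procedure is not new to the site.

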**7.1.3 Tests During the Study**

Clinical findings: subjective symptoms, objective findings

**7.1.4 Tests at the End of the Study**

At the end of each treatment phase, the principal investigator/subinvestigator will perform the following clinical observations and laboratory tests.

Clinical findings: subjective symptoms, objective findings, edema

Physical examination: body temperature (axillary), blood pressure (seated), pulse (seated)

Laboratory tests: 1) Hematology

erythrocytes, leukocytes, platelets, hemoglobin, hematocrit

2) Blood chemistry

total protein, BUN, creatinine, uric acid, AST, ALT, T-Bil, ALP, γ-GTP, Alb, PT, TC, CRP, K

**7.1.5 Identification of TJ-43 Constituents in Plasma**

Total blood drawn in this study is 524 mL {screening tests: 8 mL × 1, 172 mL for each of the 3 phases [(clinical tests: 8 mL × 2, pharmacokinetics; 12 mL × 13) × 3]}

1) Blood collection (pharmacokinetics): Sampling time

Pre-dose sample and post-dose samples at 15 min, 30 min, 1 h, 2 h, 3 h, 4 h, 6 h, 8 h, 10 h, 12 h, 24 h, and 48 h will be collected (13 total samples).

2) Method and handling of sampling

A total of 12 mL of venous blood (for the pharmacokinetic study) will be collected at one time from the subject’s antecubital vein during the sampling time, dispensed into a tube containing heparin sodium as the anticoagulant, and centrifuged at 1700 × *g* for 15 min at 4°C to obtain a plasma sample. The obtained plasma will be dispensed into tubes as needed and cryopreserved below −20°C until analysis.

3) Acceptable range and handling of sampling time error

Sampling times will be recorded at the start of collection. The acceptable sampling time windows for post-dose collection at 15 min, 30 min, and 1 h will be set within 10% of the sampling times (15 min ± 1.5 min, 30 min ± 3 min, and 1 h ± 6 min, respectively). The acceptable sampling time windows for 2-h, 3-h, and 4-h collection will be uniformly set within ±10 min (2 h ± 10 min, 3 h ± 10 min, and 4 h ± 10 min, respectively). The acceptable sampling time windows for 6-h, 8-h, 10-h, 12-h, 24-h, and 48-h collection will be uniformly set within ±30 min (6 h ± 30 min, 8 h ± 30 min, 10 h ± 30 min, 12 h ± 30 min, 24 h ± 30 min, and 48 h ± 30 min, respectively). Deviations from sampling time windows will be indicated in the CRF. Deviated samples may also be submitted for analysis. The analyzed data should be handled according to the pharmacokinetic analysis plan, which will be prepared separately.

[Rationale for Sampling Time Windows]

It was planned to collect 13 samples (12 mL each) in this study starting with pre-dose (used as a blank plasma) and at 15 min, 30 min, 1 h, 2 h, 3 h, 4 h, 8 h, 6 h, 10 h, 12 h, 24 h, and 48 h post-dose.

Based on the results of the preliminary pharmacokinetic study and existing reports19), the time to peak maximum concentration in plasma (*t*max) for most of the 8 constituents selected for quantitative analysis is within 2 h. However, it has also been confirmed that the *t*max values of naringenin and glycyrrhetinic acid are approximately between 6 and 8 h, which is relatively longer compared with the values of the other constituents. Therefore, the sampling time was determined as follows.

Considering the predicted *t*max of each of the 8 constituents, the sampling time that enables evaluation of the pharmacokinetic characteristics of each constituent was determined. Furthermore, the half-life of glycyrrhetinic acid, which has the longest half-life among the 8 constituents in this trial, is approximately 10 h; therefore, a final sampling time of 48 h after administration of the study drug was chosen so that evaluation up to 3–5 times the half-life was possible. According to the guidelines for pharmacokinetic studies in Japan, a measurement period of up to 3 times the half-life of a measured material is required, whereas sampling up to 5 times the half-life is required by the FDA. In this study, the 48-h sampling time window was planned to fulfill both guidelines.

The volume of blood to be collected was determined by considering the amount required for analysis (approximately 5 mL was calculated for each pharmacokinetic analysis, including the amount for possible reanalysis) and was decided to be 12 mL (using heparin sodium as the anticoagulant).

